## Abstract

**Background:**

With the substantially growing trend of the aging populations in China and the rest of the world, the number of total hip and total knee arthroplasty (THA and TKA) cases are increasing dramatically. It is important to develop practical strategies to improve the quality of healthcare and better outcome for patients undergoing THA and TKA. Enhanced recovery after surgery (ERAS) pathways have been reported to promote earlier recovery and be beneficial for patients. We propose the hypothesis that the ERAS pathway could reduce the length of stay (LOS) in hospital for patients undergoing primary THA or TKA.

**Methods/Design:**

This trial is a prospective, open-labelled, multi-centered, randomized controlled trial that will test the superiority of the ERAS pathway in term of LOS in hospital for the patients undergoing primary THA or TKA compared to current non-ERAS clinical practice. A total of 640 patients undergoing primary THA or TKA will be randomly allocated to either ERAS pathway (ERAS group) or conventional care according to individual participating center (non-ERAS group). The primary outcome is the total LOS in hospital; the secondary outcomes include postoperative LOS, all-cause mortality by 30 days after operation, in-hospital complications, early mobilization, postoperative pain control, total in-hospital cost, and readmission rate by 30 days after discharge from the hospital.

**Discussion:**

This trial is designed to evaluate the superiority of the ERAS pathway to conventional non-ERAS clinical practice in reducing the LOS. The results may provide new insight into the clinical applications of the ERAS pathway for THA and TKA.

**Trial registration:**

National Institutes of Health Clinical Trials Registry, NCT03517098. Registered on 4 May 2018.

## Background

Total joint arthroplasty is the definitive treatment for end-stage osteoarthritis of the hip and knee. The number of the cases increased significantly due to fast-growing aging populations around the world. It was reported that 0.33 million total hip arthroplasty (THA) and 0.7 million total knee arthroplasty (TKA) were performed in the United States annually, and the demand for the procedures were estimated at 0.57 million and 3.48 million per year in 2030, respectively [1]. It is important to establish practical strategies to improve the quality of healthcare and achieve earlier recovery and better outcome for the patients undergoing THA and TKA, while, facilitating a reduction in the heavy healthcare-related economic burden associated with the increasing number of the procedures.

Enhanced recovery after surgery (ERAS) is proposed as a series of evidence-based perioperative optimizations with multidisciplinary approach to reduce surgical stress and accelerate postoperative recovery [2]. Following the general guidelines, different ERAS pathways have been reported to reduce the morbidities, save cost, promote faster recovery, and achieve the clinical and economic gain in colorectal [3], thoracic [4], and orthopedic surgeries [5]. Regional anesthesia is recommended for ERAS because it provides reliable analgesia and little disturbance on hemodynamics in the published literature [2–4, 6]. However, for patients undergoing THA and TKA, spinal anesthesia is frequently associated with prolonged indwelling urinary catheter [7] and, furthermore, the peripheral nerve block may weaken the lower limb muscle strength, leading to delayed mobilization [8].

With the application of short-acting opioid analgesic remifentanil, and anesthetic agents including propofol, sevoflurane, or desflurane, rapid emergence from general anesthesia could be achieved without weakened muscle strength [9]. Based on the pharmacological characteristics of these agents, we propose the hypothesis that general anesthesia-based ERAS with the use of short-acting agents and without the nerve block or intrathecal analgesia could provide reduced length of stay (LOS) in hospital because of the avoidance of weakened muscle strength and possibly early mobilization.

In this trial, we develop an ERAS pathway to compare the conventional care group for patients undergoing primary THA and TKA. The aim of this trial is to scrutinize our hypothesis that ERAS could provide reduced LOS when compare with the current clinical practice.

## Methods/Design

### Trial design

The ERAS trial (http://www.clinicaltrials.gov, registration number: NCT03517098) is a prospective, randomized controlled trial that tests the superiority of the ERAS pathway to current clinical practice in term of reduction of LOS. It will be conducted under the regulations of the Declaration of Helsinki. Following the CONSORT statement (http://www.consort-statement.org/), a brief flow diagram of the ERAS trial is summarized in Fig. 1; a checklist of Standard Protocol Items: Recommendations for Interventional Trials (SPIRIT) is provided in Fig. 2. SPIRIT 2013 Checklist: Recommended items to address in a clinical trial protocol and related documents is provided in Additional file 1.

**Fig. 1 Fig1:**
[figure not shown]
Flow chart for participant eligibility, interventions, assessments, and follow-up

**Fig. 2 Fig2:**
[figure not shown]
Standard Protocol Items: Recommendations for Interventional Trials (SPIRIT) figure (numbers beside t represent days)

This trial is supported by a grant from the Key research and development (R&D) Program of Science & Technology Department of Sichuan Province (no. 2019YFS0224) and the National Natural Science Foundation of China (no. 81502722). There is no conflict of interest in the whole process of study execution. A training manual will be produced to educate and train the study team, including orthopedic surgeons, anesthesiologists, nurses, and clinical research coordinators before starting the trial.

### Sample size calculation

Our primary hypothesis is that the application of the ERAS pathway would reduce the LOS in hospital when compared to the current non-ERAS practice in total joint arthroplasty (TJA). According to retrospective analysis of LOS of in hospital of TJA in 2014 (when the ERAS pathway was just proposed) and 2016 (when the ERAS pathway was applied in about 50% of patients) in the Department of Orthopedics, West China Hospital of Sichuan University, the mean LOS of THA was 10 ± 1.5 days in 2014 and 8.6 ± 1.1 days in 2016; the mean LOS of TKA was 12.1 ± 2.1 days in 2014 and 8.9 ± 1.5 days in 2017. For THA, assuming the difference between the two groups was a 5% significance level and a power of 0.90, 17 patients in each group are required; for TKA, assuming the difference between two groups was a 5% significance level and a power of 0.90, only seven patients in each group are required for a comparison within the group. Considering an estimated 20% dropout rate, there should be 42 patients in each group for THA and 20 patients in each group for TKA; a total of 62 patients are required for this study [10]. For a better application of the ERAS pathway for orthopedic surgeons and anesthesiologists, we increased the sample size to 160 individuals in each group for THA and TKA, and a total of 640 individuals will be included. We plan to enroll 320 patients undergoing TKA to participate in this trial in the first stage and enroll 320 patients undergoing THA after completion. A primary comparison will be performed separately for TKA and THA.

### Recruitment

A total of 640 patients undergoing elective arthroplasty, 320 in THA and 320 in TKA, will be enrolled at eight hospitals in China. Individuals will be enrolled and operated in the same hospital even under potentially different conventional clinical practice.

### Randomization and blinding

We will use the Central Randomization System (CRS) to screen and randomize the patients. We will include eight hospitals as participating centers and the centers will be stratified first to guarantee balance between arms within each hospital. According to the sequence of time that the participants are enrolled, after entering the screen number and the individual’s information, the computer-based randomized number prepared on the Internet and allocated group could be retrieved on the website of the CRS. While the individuals, staff responsible for follow-up, and the statisticians will be blinded to the treatment assignment, the investigators, research assistants, and the responsible physicians will not be blinded.

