### Study organization and quality control

The principal investigator, study coordinators, and the Office of Scientific Research at West China Hospital are jointly responsible for all aspects of the study protocol and relevant amendments. The implementation of the study, data completeness, and accuracy will be supervised by the Department of Anesthesiology, West China Hospital. The data safety and monitoring board (DSMB), including an orthopedic surgeon, an anesthesiologist, a statistician, a physician, and a member from the Office of Scientific Research who are not unrelated to this trial, will be involved for the entire duration of the trial to review all investigational data for accuracy and completeness periodically to ensure protocol compliance, and to make the decision to stop the trial if there are abnormal frequencies of safety issues, or if the safety of a participant was not guaranteed because of serious complications. [name], associated professor of Department of Anesthesiology, West China Hospital, will be the personnel to alert serious complications to the DSMB and be responsible for site monitoring. Data collection and follow-up will be performed by clinical research coordinators. There will be no preliminary analysis performed before the completion of the study.

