### Interventions

#### The ERAS group

Patients will be treated according to the ERAS pathway, which is elaborated below.

ERAS pathway for orthopedic surgeons:
Preoperative fasting time: 8 h for consumption of fats and protein food, 6 h for starchy food or non-human milk, and 2 h for clear liquids before operation.Intravenous 20 mg/kg of tranexamic acid will be given 15 min before incision.No indwelling urine catheters.No tourniquet used for TKA.No drainage tube after surgery.Give low molecular heparin subcutaneously 6 h after the operation.

ERAS pathway for anesthesiologists:
Before anesthesia induction, ECG, non-invasive blood pressure, pulse oximetry, and capnogram will be continuously monitored for every patient.Intravenous 10 mg of dexamethasone immediately before anesthesia induction.Anesthesia will be induced with 0–0.2 μg/kg of sufentanil or 0–2 μg/kg of fentanyl, 0.3 mg/kg (for THA) or 0.15 mg/kg (for TKA) of cis-atracurium, and 1 mg/kg of propofol. Endotracheal intubation of insertion or laryngeal mask will be performed when the BIS value decreases to 50.Anesthesia will be maintained by titrating continuous remifentanil infusion at a range of 0.15–0.3 μg/kg.min with continuous infusion of propofol of 2–4 mg/kg/h, or keeping end- tidal desflurane (Et-Des) level at 5–7% or sevoflurane (Et-Sev) level at 1.5–2.5%. The BIS value will be kept in the range of 40–60 during the procedure.Incision site will be infiltrated with 40–50 mL of 0.2% ropivacaine at the end of the operation for postoperative analgesia; no patient-controlled intravenous analgesia devices will be applied postoperatively.

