#### The non-ERAS (Control) group

Patients undergoing THA or TKA will receive conventional care according to the individual participating center. There is no standard protocol for preoperative management, including fasting guidelines, no restriction of choices of anesthetic techniques and intraoperative medications, as well as postoperative analgesia, and indwelling urinary catheter.

For all the individuals enrolled in the study, no matter which group they are allocated, the decisions regarding whether to place the urinary catheter or drainage tube, or to use tourniquet, or to perform any other medical treatment should be made by the individual responsible physician, based on his clinical judgment. For example, if a patient is allocated to the ERAS group, but he develops urinary retention perioperatively as a result, the urinary catheter could be retained. In such case, we will make a record, and the patient will still be followed up and his data will be collected and analyzed in the ERAS group as per other individuals in the same group.

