### Outcome measures

#### Primary outcome

The primary outcome is LOS in hospital, which is defined as the time frame from the day of hospital admission to discharge from the hospital (unit: days).

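### Patients are listed as blinded in a trial called open-label, and length of stay ends at a discharge decision apparently made by unblinded physicians

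*Protocol article*

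**What the plan says.** **Blinding.** The Abstract (Methods/Design) states: "This trial is a prospective, open-labelled, multi-centered, randomized controlled trial". The Randomization and blinding section states: "While the individuals, staff responsible for follow-up, and the statisticians will be blinded to the treatment assignment", and in the same sentence that "the investigators, research assistants, and the responsible physicians will not be blinded". The Trial design section does not repeat the open-label description.

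**What patients experience.** The ERAS group section specifies a fasting schedule, general anaesthesia, no urinary catheter, no drain, and no tourniquet for knee surgery. It adds that "no patient-controlled intravenous analgesia devices will be applied postoperatively". In the control section, "Patients undergoing THA or TKA will receive conventional care according to the individual participating center", with fasting, anaesthetic technique, postoperative analgesia and catheter use left open. No masking procedure is described for either arm.

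**Primary outcome and who decides.** LOS is "defined as the time frame from the day of hospital admission to discharge from the hospital (unit: days"). The article does not name who decides discharge. The control section, speaking of both arms, says that decisions on catheter, drain and tourniquet, or "to perform any other medical treatment should be made by the individual responsible physician, based on his clinical judgment".

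**Related outcomes.** Secondary outcomes include postoperative LOS, pain scores (NRS) at rest and on mobilization, mobilization time (unaided walking) and 30-day readmission. On staffing, Study organization and quality control says: "Data collection and follow-up will be performed by clinical research coordinators".

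**The concern.** There are two linked problems.

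1. Both blinding statements are current text, and they cannot both describe the patients. NRS pain is reported by the patient, so a reader has to know whether it is a blinded outcome. If the article claims a protection that the design does not provide, the pain results will be read with too much confidence.

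2. LOS is an objective count of days, but its end point is a decision. If the person deciding knows the arm and expects ERAS patients to leave sooner, LOS can shorten without any difference in recovery. Blinding the follow-up staff and statisticians does not prevent this, because the bias would arise when discharge is decided and not when it is recorded or analysed. The Background section frames the hypothesis in terms of preserved muscle strength and earlier mobilization, so the cause of a LOS difference matters to what the trial can conclude.

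**Working it through.** **Step 1: the blinding statements.** The Abstract says open-label. The Randomization and blinding section says patients are blinded. Catheter, drain, pain pump and type of anaesthesia are all things a patient can notice, and no masking is described. Patient blinding is therefore unsupported by the article and doubtful on its own description of care.

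**Step 2: the link from blinding to LOS.** Responsible physicians are stated to be unblinded, and treatment decisions in both arms rest on their judgment. That they also decide discharge is inferred from these two statements; no other decision-maker is named.

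**Step 3: the article's own sample size.** Inputs from Sample size calculation: hip LOS 10 (SD 1.5) against 8.6 (SD 1.1) days; knee 12.1 (SD 2.1) against 8.9 (SD 1.5) days; 5% level; power 0.90. Sidedness is not stated; two-sided is assumed.

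- Pooled SD = √((s₁² + s₂²)/2). Hip: √((2.25 + 1.21)/2) = 1.315. Knee: √((4.41 + 2.25)/2) = 1.825.
- n per group = 2(1.96 + 1.2816)² SD²/δ². Hip, δ = 1.4: 2 × 10.51 × 1.73/1.96 = 18.6, so 19 (article: 17). Knee, δ = 3.2: 2 × 10.51 × 3.33/10.24 = 6.8, so 7 (article: 7).

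The inputs are close enough to the article's figures to use below.

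**Step 4: smallest observed difference that is significant at 160 per arm.** SE = SD × √(2/160).

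- Hip: SE = 1.315 × 0.1118 = 0.147; 1.96 × 0.147 = 0.29 day (0.24 to 0.33 for SD 1.1 to 1.5).
- Knee: SE = 1.825 × 0.1118 = 0.204; 1.96 × 0.204 = 0.40 day (0.33 to 0.46 for SD 1.5 to 2.1).

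The planning differences are 1.4 and 3.2 days.

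**Step 5: chance that a purely discretionary shift is significant.** Assume no true effect on recovery and a mean shift b in discharge. Probability = Φ(b/SE − 1.96). For hip with b = 0.5: Φ(3.40 − 1.96) = Φ(1.44) = 0.93. For knee: Φ(2.45 − 1.96) = Φ(0.49) = 0.69. With the article's 20% dropout, n = 160 × 0.8 = 128 per arm.

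| Assumed shift | n per arm | Hip, SD 1.315 (SD 1.5 to 1.1) | Knee, SD 1.825 (SD 2.1 to 1.5) |
|---|---|---|---|
| 0.25 day | 160 | 0.40 (0.32 to 0.53) | 0.23 (0.19 to 0.32) |
| 0.5 day | 160 | 0.93 (0.85 to 0.98) | 0.69 (0.57 to 0.85) |
| 0.5 day | 128 | 0.86 (0.76 to 0.95) | 0.59 (0.48 to 0.76) |

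The shifts are illustrations; the article gives no figure for them.

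**The case against.** The strongest reply is that the first problem is only wording and the second asks for an extra endpoint. The open-label label stands in the Abstract alone. Discharge criteria are the kind of detail a condensed article may leave to the full protocol or the training manual, neither of which is shown. That stands: the absence of discharge criteria from the article is not in itself an error.

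Four stronger readings are tempting, and the documents do not support them.

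- *Every patient will know the arm.* A control patient may have general anaesthesia, no catheter and no pump, and an ERAS patient may have a catheter or drain at the physician's judgment. The visible features are clues, not proof. Blinding is not credible as described, but it is not shown to fail for every patient.
- *The same coordinator collects ward data and makes the follow-up contact.* The article assigns both tasks to coordinators as a group and does not say that one person does both.
- *LOS cannot be separated from the decision to discharge at all.* Mobilization time has the same functional definition in both arms and does not depend on discharge, and 30-day readmission can signal premature discharge. They help, but neither measures readiness to leave. Postoperative LOS does not help, because it ends at the same discharge.
- *A half-day bias would give a positive hip result more than nine times in ten.* This fails at the larger hip SD (0.85) and after 20% dropout (0.86), and the half-day is itself hypothetical.

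A readiness measure might also be recorded by unblinded staff. That is true, though a fixed checklist leaves less discretion than a discharge date.

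**Conclusion.** The contradiction on patient blinding is certain from the text and must be reconciled. It bears directly on how NRS pain is interpreted.

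The risk to LOS is real but rests on an inference about who decides discharge. On that inference, part of a LOS difference could reflect an earlier decision rather than faster recovery, and the existing secondary outcomes answer this only partly. The enlarged sample makes the trial sensitive to small shifts: observed differences of about 0.29 day (hip) and 0.40 day (knee) reach significance at 160 per arm, well below the planning differences. The probabilities in the table assume a two-sided 5% test, the article's SDs, and a shift with no true effect. They show sensitivity to a shift and are not evidence that one will happen. A reader should not infer that a positive result would be an artefact. The point should be corrected; it does not invalidate the design.

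**What to change.** 1. In Randomization and blinding, remove the individuals from the blinded list and state that patients and treating staff are unblinded, in agreement with the Abstract. Report NRS pain as an unblinded outcome.
2. Leave the discharge decision with whoever makes it now. In both arms, have the existing coordinators record when one prespecified, identical readiness checklist is first met. Its content is for the investigators to set.
3. Report time to readiness with the same model as LOS, as a supportive analysis, and read it alongside mobilization time and 30-day readmission.
4. Where existing staffing allows, have the 30-day follow-up calls made by staff without ward contact.

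Cost: a wording change and a short daily record at eight hospitals. The remaining weakness is that readiness may itself be recorded unblinded, which the report should say.

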#### Secondary outcomes

i.Postoperative LOS, which is defined as the time frame from the day of operation to discharge from the hospital (unit: days).ii.All-cause mortality by 30 days after operation.iii.In-hospital complications, which are divided into five grades:
Grade I: recovery after temporary treatment, e.g. postoperative nausea and vomiting (PONV), postoperative anxiety, insomnia.Grade II: prolonged hospitalization, e.g. pulmonary infection requiring antibiotics or other treatment, surgical wound infection requiring wound debridement.Grade III: life-threatening complications requiring intense treatment during hospitalization and resulting in good functional recovery, e.g. dialysis therapy for acute renal insufficiency, mechanical ventilatory support for respiratory failure, or postoperative bleeding requiring re-operation.Grade IV: life-threatening complications resulting in significantly decreased quality of life, e.g. myocardial infarction, stroke that left paralytic limbs.Grade V: all-cause mortality by 30 days after operation, which is defined as a secondary outcome.iv.Mobilization time, which is defined as the time frame from the end of operation to the ability to walk without external assistance (unit: hours).v.Numerical rating scales (NRS) scores at rest during three days after operation.vi.NRS scores during mobilization or physical therapy during three days after operation.vii.Postoperative sufentanil or other analgesics requirement during three days after operation.viii.Total in-hospital cost.ix.Readmission rate by 30 days after discharge from the hospital.

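### The protocol lists participants as blinded, but it calls the trial open-label and describes pathways that many awake patients could tell apart, so participant blinding is not supported

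*Protocol article*

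**What the plan says.** The abstract of the protocol article (Methods/Design) states: "This trial is a prospective, open-labelled, multi-centered, randomized controlled trial". The section Randomization and blinding then divides the people involved into two lists. The blinded list reads: "While the individuals, staff responsible for follow-up, and the statisticians will be blinded to the treatment assignment". The unblinded list reads: "the investigators, research assistants, and the responsible physicians will not be blinded".

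The section on the ERAS group sets out what patients in that arm receive. It allows clear liquids until 2 h before operation, uses general anaesthesia, and specifies "No indwelling urine catheters.No tourniquet used for TKA.No drainage tube after surgery". It also says that "no patient-controlled intravenous analgesia devices will be applied postoperatively". The section on the non-ERAS (Control) group leaves care to each centre, with "no restriction of choices of anesthetic techniques and intraoperative medications, as well as postoperative analgesia, and indwelling urinary catheter". It adds that in both groups the responsible physician decides on catheter, drain and tourniquet.

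The secondary outcomes include pain scores at rest, "NRS scores during mobilization or physical therapy during three days after operation", analgesic requirement over the same three days, and the time from end of operation to walking unaided. The Statistical analysis section tests secondary outcomes at p < 0.05.

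**The concern.** The open-label description and the blinded list disagree about the participants. The word individuals cannot easily be read as anyone else: the sentence before it in Randomization and blinding uses it for the person being enrolled, and the Recruitment section uses it for those enrolled and operated on.

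Pain scores are the patient's own report. Analgesic requirement depends partly on what the patient asks for, and time to unaided walking partly on the patient's effort. If participants are taken to be blinded, a difference between arms on these outcomes can be read as free of expectation effects. If many of them can recognise their pathway, that reading is not available. At stake is what the secondary pain results can be said to show, and whether the blinding status carried into the trial report is accurate.

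**Working it through.** No figure in the protocol bears directly on this point, so the main check sets the statements side by side.

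**Step 1: the two descriptions of the trial.** The abstract says open-labelled. Randomization and blinding says participants, follow-up staff and statisticians are blinded. Open-labelled could be loose shorthand for unblinded physicians. In that case the article still makes a specific claim about participants, and that claim has to be compared with the interventions.

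**Step 2: what an awake patient could notice.**

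| Feature | ERAS arm | Control arm | Noticeable to the patient? |
|---|---|---|---|
| Clear liquids before surgery | Allowed until 2 h before | Centre's practice, no standard | Yes, where practice differs |
| Urinary catheter | None planned | Unrestricted | Yes, but physician may override in either arm |
| Drain | None planned | Physician's decision | Yes, but physician may override in either arm |
| Patient-controlled analgesia device | None | Postoperative analgesia unrestricted | Yes, where the centre uses one |
| Type of anaesthesia | General | Unrestricted | Yes, where the centre uses spinal anaesthesia or a nerve block |
| Tranexamic acid, dexamethasone, tourniquet, wound infiltration | As specified | Centre's practice | Much less so; given around or during surgery |

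Several of the differences are open to view. The Background section gives avoidance of weakened muscle strength after nerve block or intrathecal analgesia as a reason to expect benefit. A control patient with such a block could feel that difference.

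**Step 3: which outcomes are exposed.** Pain at rest and on movement is fully self-reported. Analgesic requirement is partly patient-driven. Mobilization time is defined by an ability that staff can observe, so it is less exposed. Thirty-day mortality is hardly exposed at all.

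**Step 4: an illustration of sensitivity to bias.** Inputs: n = 160 per arm within each of the TKA and THA comparisons (Sample size calculation), and a 5% level (Statistical analysis; two-sided is assumed, as the section does not say). The size of any reporting bias, b, in SD units, is an assumption. The calculation uses a normal approximation to a two-sample comparison.

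- Standard error in SD units: √(2/160) = 0.1118.
- Smallest difference reaching p < 0.05: 1.96 × 0.1118 = 0.22 SD.
- With no true effect and bias b, P(p < 0.05) = Φ(b/0.1118 − 1.96) + Φ(−b/0.1118 − 1.96).

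| Assumed bias b | b/0.1118 | P(p < 0.05) |
|---|---|---|
| 0 | 0 | 0.050 |
| 0.1 SD | 0.894 | 0.145 |
| 0.2 SD | 1.789 | 0.432 |
| 0.3 SD | 2.683 | 0.765 |

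The probability is the same whichever arm the bias favours.

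**The case against.** The strongest reply is that the pathways overlap. The control section does not say that controls get a catheter, drain, pump or regional anaesthesia; it leaves these open. Physicians may place a catheter or drain in either arm. A control patient could have general anaesthesia and no pump, and would have little basis for guessing. This stands. A reader might infer that every patient can see their allocation, and the documents do not support that. They support only that many could, and that the article shows nothing that would prevent it.

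A second reply is that the article condenses a longer protocol and may leave out how allocation is withheld. This also stands as far as it goes, so the lack of a described concealment method should not carry the point by itself. The conflict between the open-label description and the blinded list remains. An unshown procedure would also hardly hide a catheter, drain or pump from the patient who has one. The consent form is not shown, so nothing can be argued from its content.

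A third reply is that the sections on secondary outcomes and statistical analysis never describe the pain or walking outcomes as blinded. That is correct. The risk lies in how the results will be read given the stated blinding.

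Finally, the direction of any bias is not known. Patients may expect more of an enhanced pathway, but those without a pump may expect worse pain control.

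**Conclusion.** The point holds in a limited form. Participant blinding is a stated property that conflicts with the abstract and that the described interventions do not support. It affects the interpretation of secondary outcomes: chiefly the pain scores, then analgesic requirement, and to a lesser degree mobilization time.

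The size of any resulting bias cannot be derived from the documents. The figures of about 14.5%, 43% and 77% rest on assumed biases of 0.1, 0.2 and 0.3 SD, a two-sided 5% test, 160 analysed per arm and a normal approximation. A Wilcoxon test, which the plan allows, or a different handling of the three days of scores would change them somewhat. They show only that a sample of this size would declare small biases significant. A reader might take them as the expected false-positive rate of the trial, or infer that the analysis depends on participant blinding; the documents support neither.

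The point does not dispute the blinding of the statisticians, and it makes no claim about the follow-up staff or the primary outcome.

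**What to change.** 1. In Randomization and blinding, remove the participants from the blinded list and state that they are not blinded, in agreement with the abstract.
2. In Secondary outcomes and Statistical analysis, identify pain at rest, pain on movement, analgesic requirement and, with less weight, mobilization time as outcomes open to expectation bias. State that they will not be presented as participant-blind evidence of better pain control.

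The cost is a few sentences of protocol text. No change to the interventions, sample size or tests is needed. The downside is that the secondary pain results will be described less favourably.
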